## Abstract

**Background:**

It seems that lumen-apposing metal stents (LAMS) are displacing plastic stents in the therapy of pancreatic-fluid collection in walled-off necrosis (WON). To date, there is no quality of evidence to recommend LAMS as the standard treatment in the management of WON. The theoretical benefit of LAMS over plastic stents needs to be proven.

**Methods/design:**

This is a randomized controlled, multicenter, prospective clinical trial with two parallel groups, without masking. One-hundred and fourteen patients with WON will undergo endoscopic ultrasound (EUS)-guided transmural draining in nine tertiary hospitals in Spain and will be randomized to the LAMS or plastic-stent group. The primary endpoint is the short-term (4 weeks) clinical success determined by the reduction of the collection (to < 50% or < 5 cm in size), along with clinical improvement. Secondary endpoints: long-term (4 months) clinical success (total resolution or 5 cm), procedure duration, level of difficulty, safety, and recurrences.

**Discussion:**

The PROMETHEUS trial has been designed to determine whether LAMS are superior to plastic stents in EUS-guided transmural drainage of WON.

**Trial registration:**

ClinicalTrials.gov, ID: NCT03100578. Registered on 4 April 2017. https://clinicaltrials.gov/ct2/home

## Background

The Atlanta classification of pancreatic-fluid collection establishes that walled-off necrosis (WON) consists of a variable amount of necrotic tissue within a reactive-tissue wall. This derives from the encapsulation of acute necrotic collections. Imaging tests reveal a well-defined wall surrounding the collection, the formation of which typically occurs at about 4 week from the origin of the acute or chronic pancreatitis. The presence of more necrosis worsens the prognosis; mortality in patients with necrotizing pancreatitis is as high as 15%, and it can reach 30% in patients with infected necrosis [1, 2]. In case of symptomatic WON, drainage is considered, and in the last two decades minimally invasive approaches (surgical or endoscopic) have enjoyed increased acceptance in the management of necrotic collections over open surgical necrosectomy, with fewer adverse events (AEs) and less long-term morbidity. Recent trials have shown that endoscopic approaches offer better clinical outcomes, with improvement in quality of life and lower costs [3–6].

In the last few decade, endoscopic techniques, such as the use of endoscopic ultrasound-guided transmural drainage, have been increasingly used as a first-line option for the treatment of symptomatic WON [5, 7]. To date, plastic stents (such as double plastic stents) have been become the mainstay of endoscopic therapy for WON, until the introduction of lumen-apposing metal stents (LAMS) [8–10]. There is the hypothesis that the large diameter of LAMS improves the drainage of WON with respect to plastic stents (7–10 Fr) and carries less time-consuming interventions, with a smaller number of endoscopic procedures to achieve final success. Regarding safety, the risk of leakage, perforation, or migration would theoretically be reduced using the specific stent design of LAMS. However, LAMS are more expensive, and their safety is controversial, with a significantly higher rate of AEs, such as bleeding, compared with plastic stents [11–14] (Table 1).

Although some international systematic endoscopic reviews and meta-analyses have recommended LAMS as the care standard for WON drainage, the quality of evidence is not high (retrospective, registry-based, or non-comparative) that LAMS are superior to PLASTIC stents in the management of WON by EUS-guided transmural drainage, and few studies have compared LAMS and plastic stents [15–20]. For all these reasons, a multicenter, prospective, parallel-group, randomized controlled clinical trial was designed to assess whether LAMS are superior to plastic stents in the endoscopic treatment of WON.

## Methods/design

The PROMETHEUS trial is a randomized controlled, multicenter, prospective clinical trial with two parallel groups, without masking and with a 1:1 allocation ratio. One hundred and fourteen patients with WON will be scheduled for endoscopic ultrasound (EUS)-guided transmural drainage in nine tertiary Spanish hospitals and will be randomized to the LAMS and plastic-stent groups. All the centers are members of the Spanish Society of Digestive Endoscopy (SEED), which acts as the promoter of this trial.

Central ethical approval of the study protocol has been confirmed from the Comité Ético de Investigación Clínica (CEIC) del Hospital Universitari de Bellvitge-IDIBELL (ref approval no. 140/15) and we will not begin recruiting at other centers in the trial until local ethical approval has been obtained. A Standard Protocol Items: Recommendations for Interventional Trials (SPIRIT) Checklist is attached as Additional file 1.

**Table 1 Tab1:** Comparative table of the two kinds of stents used in transmural drainage of pancreatic collections

Lumen-apposing metal stent		Plastic	
Advantages	Disadvantages	Advantages	Disadvantages
Easy release	Expensive	Economical	Smaller diameter
Wide diameter	Less scientific evidence	Easy extraction	Shorter patency
Better drainage of solid waste and necrosis	Temporary placement	May be left permanently in place	High occlusion rate
Direct necrosectomy via stent	Traumatism caused by the ends	Greater experience (studies)	A single stent is not enough for WON
Longer patency	Not known whether permanent placement is possible	High success rate (> 80–90%, all types of collections)	Multiple > demanding technique (MTGT for WOPN)
Correct visibility			Worse visibility (fluoroscopy)
Short therapeutic time			
Hemostatic effect			
Prevents migration			Leakage of liquid (in ostomy)
Anchoring effect			
Prevents liquid leakage			Migration
Easy extraction			

*MTGT* Multiple transluminal gateway technique, *WOPN* Walled-off pancreatic necrosis

### Study population

This clinical trial will be performed at the endoscopy unit of the digestive diseases departments of nine tertiary and university centers in Spain. In order to participate in this study, the patient must be a candidate for guided transmural drainage with EUS of WON-type pancreatic collection as a local complication in acute pancreatitis. The investigator at each center will be contacted to evaluate the inclusion of the patient in the study. The patient will be correctly informed by personnel knowledgeable about the specifics of the study, who will help to resolve any questions that may arise. The informed consent form will be signed in the presence of participating personnel knowledgeable about the study. The patient has the right to opt out of the study at any time.

The inclusion and exclusion criteria are listed in Table 2.

**Table 2 Tab2:** Selection criteria for WON walled-off necrosis. ^a^Diagnosis of WON based on imaging procedures

Inclusion criteria:	
*Patients eligible for the trial must comply with all of the following at randomization* • Age 18 years or older • Patient with indication (ASGE, Jacobson BC, GIE2005) of drainage of only one type^a^ related to the symptomatology, as a local complication of previous acute pancreatitis • Patient capable of understanding and signing informed consent form • Patient understanding the type of study and complying with the follow-up of complementary tests during the study’s duration	
Exclusion criteria	
• Pregnancy or breast-feeding • Severe coagulation disorder: INR > 1.5 not correctible with administration of plasma and/or platelets < 50,000/mm^3^ • Asymptomatic patients, without clinical indication of drainage, except for those with vascular compression involvement • Non-identification of solid content during EUS procedure • Failure to sign informed consent form • Patients with intellectual handicap who are unable to understand the nature and possible consequences of the study, unless there is a competent legal representative • Patients unable to adhere to subsequent follow-up requirements • Conditions that preclude upper digestive endoscopy, such as stenosis	

*Note*: If there are several pancreatic collections, this does not exclude the patient from the trial. The patient is only excluded if there is more than one symptomatic collection to be drained

*EUS* endoscopic ultrasound, *INR* international normalized ratio

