### Randomization and masking

Patients will be enrolled in this trial by gastroenterologists, surgeons, and endoscopists who will evaluate the cases in the inpatient wards or in the outpatient consultation areas. The participants will be randomized with a random-number table generated by an online platform.

A code list will be generated by randomization with a 1:1 randomization ratio, by blocks, stratified by centers and by American Society of Anesthesiologists’ classification (ASA) score. Each individual will be assigned a randomization code along with the treatment that corresponds. Once the patient meets the eligibility criteria and has provided informed consent, we will proceed to the allocation of each participant centrally, ensuring allocation concealment, and based on the randomization list. To prevent different subject recruitment rates at the various hospitals from interfering with the development of the study, the entire population will be randomized in blocks of four between the two treatment possibilities.

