#### General description of the technique

Each selected case will ensure a conclusive diagnostic revision with WON. In case of doubt, EUS-guided, fine-needle aspiration will be considered prior to drainage to rule out cystic tumor. Prophylactic antibiotic therapy will be administered in accordance with the protocol of each center. In case of INR > 1.5, this will be corrected in accordance with the protocol of each center until INR < 1.5. Procedures will be performed under deep sedation in accordance with the directives of each center. In case of collection > 10 cm (> 700 mL), tracheal intubation by anesthesiologist is recommended. Carbon dioxide insufflation is recommended, especially for endoscopic necrosectomy. The WON will be localized by using a linear echoendoscope, selecting the appropriate optimal region for carrying out the EUS-guided puncture. The collection will be punctured with a 19-G needle (plastic or LAMS group) or directly with an electrocauterizing device (freehand technique, only in the LAMS group). The guidewire will be advanced and coiled into the WON cavity. Then, the transmural ostomy will be carried out in accordance with the normal procedure of the experienced endoscopist. The use of a fluoroscope will be decided upon on the basis of technical considerations and the opinion of the endoscopic interventionist. The use (or not) of a fluoroscope will be noted in the case report form (CRF). The scale of the ostomy will be determined by the size of the collection (see Table 3).

**Table 3 Tab3:** Number of stents along with technical variations depending on size of WON, observed with EUS during procedure

Type	LAMS (*n*, ø)	Plastic (*n*, ø)
WON < 10 cm	1, 10–15–20 mm	≥ 1, minimum 1 of 10Fr (+ ostomy 8–10 mm)
WON > 10 cm	≥ 1, > 15 mm	≥ 2, minimum 1 of 10Fr (+ ostomy 10–15 mm)

*LAMS* lumen-apposing metal stent; *WON* walled-off necrosis, *FR* French

After the interventional procedure, all inpatients cases will be returned to the hospital ward and will discharged after clinical improvement. Outpatients will spend a minimal of 24 h under observation and will be discharged the next day unless there is no improvement of symptoms or the appearance of AEs.

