#### Additional comments

In the event of technical failure in the placement of the stent (plastic or LAMS) for any reason, alternative treatment will be decided upon in accordance with the directives of the endoscopic interventionist, with the aim of offering the patient the best possible solution.

The first controls will be on the first day following and at 4 weeks (see Table 4). If there is no short-term clinical success, the most beneficial therapeutic approach for the patient will be adopted in accordance with the criteria of the patient’s medical team (for example: the use of technical variants at initial drainage such as placement of coaxial plastic pigtail within the LAMS, replacement or change the stent type, use of nasocystic drainage or other known variants).

**Table 4 Tab4:** Data management, calendar

Timepoint/stages	Study Period									
	Baseline	Intervention	24 h	7 days ±	4 weeks ± 3 days	8 weeks ± 5 days (Telephone)	16 weeks (4 months) ± 10 days	6 months ± 10 days (Telephone)	8 months ± 10 days	12 months ± 10 days (Telephone)
Enrollment										
Informed consent	X									
Clinical history and exploration	X									
Eligibility screen	X									
Allocation	X									
Intervention										
Implantation		X								
Removal					X					
INR		X								
Assessments:										
Blood test	X		X		X		X		X	
Imaging test	X	X			X	X^a^	X		X	
Symptomatology	X		X	X	X	X	X	X	X	X
Visit			X		X		X		X	
Telephone contact				X		X		X		X
Adverse effects	X	X	X	X	X	X	X	X	X	X
Primary outcome					X					
Secondary outcomes					X					
Medication	X	X	X	X	X	X	X	X	X	X

^a^Only in case of radiological clinical success but with persistence of the collection > 5 cm

Every intervention, diagnostic procedure, and additional therapeutic contribution will be noted in the CRF.

In the case of collections of significant size (i.e., 14 cm) with clinical-radiological success but without the disappearance of the collection (i.e., CTMD reduction from 14 to 6 cm), precluding the removal of the stent, a new CTMD will be performed at 4 weeks (8 weeks) to assess removal of the stent.

Therefore, the removal of a stent is contemplated when there is disappearance of the collection or a decrease < 5 cm.

Patients will remain in the hospital for a minimum of 24 h for clinical observation, under medical supervision.

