### Definitions

The term WON is in accordance with the literature (latest revision of Atlanta, Banks PA et al. Gut 2013) [1]. At least two imaging tests will be required (CTMD, MRI, EUS) prior to the transmural drainage, the results of which must be in agreement on the classification of the collection as WON.

Technical success is defined as the correct release of the stent at both ends, with observed drainage of the liquid.

Clinical success is defined as the significant reduction of the collection along with clinical resolution.

Recurrence is defined as a symptomatic pancreatic collection diagnosed with imaging test during the follow-up of prior procedure with initial clinical success.

AEs are defined as undesirable situations suffered by patients during the study, whether related or not to the EUS-guided transmural drainage with a stent (plastic or metal). All AEs referred by patients or observed by the medical team will be duly documented. All serious AEs will be detailed, and the study promoter/principal investigator will be notified within 7 days. In the event of a death, notification will be made within 24 h. AEs will be recorded in both the clinical history of the patient and the CRF, with appropriate medical terminology. Whenever possible, the diagnosis rather than the symptoms will be recorded. These guidelines are to be followed from the time of the signing of informed consent until 30 days after the final visit in the study calendar. AEs will be classified as mild, moderate, serious, or fatal, in accordance with the nomenclature for AEs in endoscopy (ASGE Workshops 2010, Cotton GIE 2010; 71:446–54). The determination as to whether an AE is related to the EUS-guided transmural drainage with stent (plastic or metal) will be made by the patient’s medical team, the local investigator, and the principal investigator of the study.

In Additional file 2 is included information about AE definitions and MEDDEV guidelines. “Research product security surveillance” section, according to the definitions set out in the MEDDEV 2.7/3 guidelines (rev 3, May 2015) “Guidelines on medical devices: Clinical investigations: Serious adverse event reporting under Directives 90/385/EECC and 93/42/EEC” (Additional file 2).

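### Solid content on EUS is an exclusion criterion, but the calendar allocates at Baseline, so some patients could be excluded after allocation by an operator who knows the arm

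*Protocol article*

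**What the plan says.** All references are to the protocol article.

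- **Study population, Table 2.** The inclusion list applies at a fixed moment: "Patients eligible for the trial must comply with all of the following at randomization". One exclusion criterion is "Non-identification of solid content during EUS procedure".
- **Randomization and masking.** Enrolling clinicians "evaluate the cases in the inpatient wards or in the outpatient consultation areas". The order is then given as: "Once the patient meets the eligibility criteria and has provided informed consent, we will proceed to the allocation of each participant centrally".
- **Additional comments, Table 4 ("Data management, calendar").** Consent, eligibility screen and allocation are all marked in the Baseline column. Implantation is marked in the next column, Intervention.
- **Definitions.** "At least two imaging tests will be required (CTMD, MRI, EUS) prior to the transmural drainage", and their results must agree that the collection is WON.
- **General description of the technique, Table 3.** Similar wording is used for the drainage session: "Number of stents along with technical variations depending on size of WON, observed with EUS during procedure".
- **Methods/design.** The trial is described as "with two parallel groups, without masking and with a 1:1 allocation ratio".

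**The concern.** An eligibility criterion should be settled before the arm is known. Here one criterion is worded as a finding made during an EUS procedure, while allocation is scheduled at Baseline. For a patient who has not had an earlier EUS, the criterion would be read at drainage, after allocation. The operator cannot be unaware of the arm at that point: the equipment differs, and direct electrocautery puncture is allowed only in the LAMS group.

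Whether solid content is seen is partly a matter of judgement, and the protocol itself treats it as relevant to outcome. The Background says that more necrosis worsens prognosis, and Table 1 lists better drainage of solid material among the advantages of LAMS. If the judgement were made differently according to which stent was waiting, the two groups would no longer be the groups that randomisation formed. Even if it were applied evenly, patients removed after allocation and not replaced would reduce the number analysed.

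**Working it through.** **Order of events.** The rule in Randomization and masking (eligibility, then allocation) and the Baseline allocation in Table 4 can both hold only if solid content has been assessed on EUS by Baseline. There are two routes.

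1. *EUS is one of the two pre-drainage imaging tests, done before allocation.* The criterion can be read in time and no problem arises.
2. *The two tests are CTMD and MRI.* This meets the Definitions section. The first EUS may then be the one at drainage, in the Intervention column. On the Table 4 schedule, allocation has already taken place.

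Nothing in the article closes the second route. It does not require an EUS before allocation, and it does not say that allocation waits for the EUS finding.

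**The plan's own figure.** Inputs from Sample-size calculation: success 0.75 and 0.50, power 80%, type I error 5% (two-sided assumed). With pooled variance under the null and no continuity correction:

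n = [1.96·√(2 × 0.625 × 0.375) + 0.8416·√(0.1875 + 0.25)]² / 0.25² = (1.342 + 0.557)² / 0.0625 ≈ 57.7, so 58 per arm.

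The plan states 57, which gives 79.5% power before loss. The stated size reproduces to within one patient and is not at fault on this point.

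**Illustrative worst case.** The documents give no rate of absent solid content and no success rate for such patients. Assume a share f of 5–10%, and success s of 80–90% among them. Suppose all are dropped from the plastic arm and none from the LAMS arm. With planned plastic success of 0.50:

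observed success = (0.50 − f·s) / (1 − f)

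| f | s | Observed plastic success | Shift |
|---|---|---|---|
| 0.05 | 0.80 | 0.460/0.95 = 0.484 | 1.6 points |
| 0.05 | 0.90 | 0.455/0.95 = 0.479 | 2.1 points |
| 0.10 | 0.80 | 0.420/0.90 = 0.467 | 3.3 points |
| 0.10 | 0.90 | 0.410/0.90 = 0.456 | 4.4 points |

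If true success were 0.50 in both arms and s = 0.90, the two-sided type I error would rise from 5% to about 5.6% (f = 0.05) or 7.5% (f = 0.10). This uses a normal approximation with 57 LAMS patients and 57(1 − f) plastic patients, and ignores the interim analysis.

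**Direction.** If the same patients were dropped from the LAMS arm only, its planned 0.75 would become (0.75 − 0.05 × 0.8)/0.95 = 0.747 or (0.75 − 0.10 × 0.9)/0.90 = 0.733. That is a shift of 0.3 to 1.7 points against LAMS. The sign depends on which arm loses patients.

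**Even exclusion.** If f applied equally to both arms, and these patients left the main analysis without replacement, power would fall from 79.5% to 77.4% (54.15 per arm) or 75.1% (51.3 per arm), before the planned 5% loss. That is 5.7 to 11.4 of 114 patients.

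**The case against.** The strongest reply is that the protocol's explicit rule already puts eligibility before allocation, and that Table 4 is a visit grid that gives no interval between Baseline and Intervention, so both could fall on the same day. The intention is therefore probably right. The rule does not say how it is met for a criterion worded as a finding during a procedure, when patients are assessed in wards and clinics and allocation is marked at Baseline. The passages still need reconciling.

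Several stronger readings are tempting, and the documents do not support them.

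- *That the criterion can only be read at the drainage session.* EUS is one of the permitted imaging tests before drainage, Table 4 marks imaging at Baseline, and EUS-guided aspiration before drainage is foreseen in doubtful cases. The gap concerns patients without an earlier EUS. Agreement of two tests on WON may also leave few collections without solid content.
- *That allocation concealment is defeated.* Concealment protects the sequence up to assignment, and allocation is central. Exclusion after assignment is a different bias.
- *That INR raises the same problem because it is marked at Intervention.* Table 4 also has a Baseline blood test, only a non-correctible INR excludes, and the value is objective. The Intervention mark fits a re-check.
- *That such patients will leave the main analysis.* The Data management section removes major deviators from what is probably the per-protocol set. Handling of ineligible allocated patients may be settled in the statistical analysis plan, so silence on it here is not a defect.

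It also stands that one-arm exclusion is an extreme. If exclusion is even across arms, the differential bias largely disappears.

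**Conclusion.** The point holds as an inconsistency in timing. Table 2, Table 4 and the randomization section, read with the optional EUS in the Definitions, allow a patient classified by CTMD plus MRI to be allocated before the solid-content criterion is read, and then to be excluded by an unmasked operator. What is shown is an opportunity, not an expected bias.

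A reader might infer from the worst case that the trial is tilted towards LAMS. The documents do not support that: they give neither the frequency of such findings nor any sign that they would be handled differently by arm. The 1.6 to 4.4 points rest entirely on the assumed 5–10% frequency, the assumed 80–90% success, and exclusion from the plastic arm alone. They are small beside the planned 25-point difference. The correction is worth making because it is cheap and removes the route altogether.

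**What to change.** Reconcile Table 2, Table 4 and Randomization and masking so that they describe one sequence: solid content is confirmed on EUS and recorded, and only then is central allocation requested. The EUS may be a prior diagnostic examination or, where there was none, the start of the drainage session before puncture. In Table 4, the allocation mark would follow this check.

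Add that every allocated patient stays in the main analysis in the allocated arm, and that any later finding of no solid content is reported by arm.

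The cost is modest. Allocation is already central, both stent types must already be available at each site, and the stratification factors (center and ASA score) are known beforehand. The downside is that allocation is requested later, so it must be obtainable at the time of the procedure when no earlier EUS was done; the article does not say whether it is. As recruitment began in June 2017, the change would also need an amendment notified to AEMPS and the ethics committees, as with the previous ones.
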